#### **10.1.1 Detecting AEs, ARs SAEs and SARs**

All adverse events (including adverse reactions, serious adverse events and unexpected) must be recorded from the time a participant signs the consent form to take part in the study until the last follow up (18 months). (Expected events from having a pessary are recorded on study specific CRF's and not recorded as additional AEs).

In the standard care group, the local TOPSY research team will ask about the occurrence of AEs/SAEs at every pessary follow up appointment. Open-ended and non-leading verbal questioning of the participant will be used to enquire about AE/SAE occurrence. Participants will also be asked if they have been admitted to hospital, had any accidents, used any new medicines or changed medication regimens. If there is any doubt as to whether a clinical observation is an AE, the event should be recorded. Women in the self-management group are asked during the teaching appointment and advised in the information leaflet to call the telephone helpline if they experience any of the symptoms that may be indicative of an SAE/AE. The Pessary complication questionnaire completed by all women at all time-points will also capture any adverse events experienced.

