| Pessary confidence questionnaire (to measure pessary-specific self-efficacy)     | X                          | X        | X         | X         |
| Health Resource Questionnaire (uptake of additional prolapse treatment /support) |                            | X        | X         | X         |
| Telephone Support log (uptake of telephone support related to pessary use)       | Continuous data collection |          |           |           |
| Adherence to randomised protocol                                                 | Continuous monitoring      |          |           |           |

|                                                            |                                                            |  |  |   |
|------------------------------------------------------------|------------------------------------------------------------|--|--|---|
| Health of vaginal tissues (Vaginal examination in clinic)* | X                                                          |  |  | X |
| COVID-19 Survey**                                          | Completed at first clinic visit once services have resumed |  |  |   |

\* Women in standard care group will have vaginal tissues assessed at each clinic appointment as per standard practice. Women in the self-management group will have their vaginal tissues assessed at baseline and 18 month appointments.

\*\* This will only be completed by women who had a standard care or 18 month appointment cancelled/postponed due to COVID-19. It may be posted/emailed out to women with their next due questionnaire booklet if centres have specific resource issues where this can't be completed at the first clinic visit (post COVID).

After the participants have consented, demographic and medical history data will be collected. Outcome measures on which data will be collected are described in the sections below.

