#### **Pessary Complications Questionnaire**

A new pessary questionnaire (with 15 possible complications of pessary use), developed based on the literature, PPI opinion, and the team's experiences in the pilot study, will be used to assess women's pessary complications (e.g. discharge, odour, pain, discomfort, bleeding). Pessary complications are used to assess impact and safety of the trial interventions.

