|--------------------------------------------------------------------------------------------------------------------------------------------|------------------------------------------------------------|--------------------------------------------------------------------------------------------------------------------------------------------|------------------------------------------------------------|
| telephone/ e-mail contact with healthcare)                                                                                                 |                                                            | telephone/ e-mail contact with healthcare) )                                                                                               |                                                            |
| Follow-up appointment at 18 months
(with who, for how long, record any treatment given or new pessary)                                  | Patient records.
Recorded on CRF.                       | Follow-up outpatient appointment at 6, 12, 18 months
(with who, for how long, record any treatment given or new pessary)                | Patient records.
Recorded on CRF.                       |
| Out of pocket expenditure related to prolapse or pessary

Travel, time off work, parking, childcare to attend follow up appointments | Participant-completed questionnaire at 6, 12 and 18 months | Out of pocket expenditure related to prolapse or pessary

Travel, time off work, parking, childcare to attend follow up appointments | Participant-completed questionnaire at 6, 12 and 18 months |

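### Clinic-recorded adverse events are actively sought at each standard-care appointment but rest mainly on the woman's own call in self-management until 18 months; only the questionnaires and the 18-month examination are equal between arms

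*Protocol*

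**What the plan says.** Section 10.1.1 describes detection arm by arm. For standard care: "In the standard care group, the local TOPSY research team will ask about the occurrence of AEs/SAEs at every pessary follow up appointment". For self-management: "Women in the self-management group are asked during the teaching appointment and advised in the information leaflet to call the telephone helpline" if they have symptoms that might indicate an event. The same section then adds a source common to both arms: "The Pessary complication questionnaire completed by all women at all time-points will also capture any adverse events experienced".

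Examination differs in the same direction. The footnote to Table 7.1 says "Women in standard care group will have vaginal tissues assessed at each clinic appointment as per standard practice", and then "Women in the self-management group will have their vaginal tissues assessed at baseline and 18 month appointments". Table 7.2 lists "Follow-up outpatient appointment at 6, 12, 18 months" for standard care and "Follow-up appointment at 18 months" for self-management.

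Section 7.1.3 describes the complications questionnaire as covering 15 possible complications and gives its purpose: "Pessary complications are used to assess impact and safety of the trial interventions". Table 7.1 schedules it at baseline, 6, 12 and 18 months for everyone.

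**The concern.** Self-management removes interim clinic visits, so a reader will want to know whether problems increase when those visits go. Section 13 itself links the most serious complications to a pessary left in place for a long time. If staff ask about events, and look for them, more often in one arm, that arm will tend to record more events even when true rates are equal. A real excess in self-management could be hidden in the same way.

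Unequal counts can mislead without a formal test. Under section 9.5 the DMEC reviews accumulating safety data and may advise stopping for harm or benefit. Under section 8.3 complications and adverse events feed the decision model. The imbalance lies in how the data are collected, so an analysis plan cannot recover events that were never asked about.

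**Working it through.** **1. What the plan quantifies.** It gives no AE rate and no detection rate. The only stated figure used here is the group size, which reproduces: 2 × (1.960 + 1.282)² × 50² / 20² = 131.4, so 132 per group, and 132 / 0.80 = 165.

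**2. Scheduled clinic contacts over 18 months.** Table 7.2 gives three in standard care and one in self-management. The 18-month visit is shared, so the scheduled excess is two interim visits. Section 10.1.1 does not expressly say that AE questions are put to self-management women at 18 months; I assume they are. Standard care follows local practice (section 6.2), so the excess varies. With changes every 6 months the interim visits fall at months 6 and 12 (two). Every 4 months gives months 4, 8, 12 and 16 (four). Section 1 reports a practice range of 3 to 12 months, which gives five interim visits down to one.

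**3. Sources set side by side.**

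| Source | Standard care | Self-management |
|---|---|---|
| Staff enquiry about AEs | Every pessary follow-up | None stated before 18 months |
| Helpline call by the woman | Possible through the local team | Main route for reporting AEs |
| Two-week call (section 6.1) | No | Yes; stated content is pessary handling and difficulties |
| Interim tissue examination | Each appointment | Not scheduled |
| 18-month examination | Yes | Yes |
| Complications questionnaire, 15 items | Baseline, 6, 12, 18 months | Same |
| Resource-use items, pessary or prolapse care | 6, 12, 18 months | Same |

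Two gaps remain after the shared rows are counted. First, section 10.1 counts any untoward occurrence that led the woman to seek professional advice, and any hospitalisation after randomisation that was not already planned. The shared questionnaires are limited to pessary complications and pessary- or prolapse-related care. Second, erosion or ulceration counts as an adverse reaction only once a clinician has diagnosed it, so interim cases can be found routinely in standard care only.

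There is also a gap in the route to assessment. The local PI records and assesses AEs (sections 10.1.2 and 10.1.3), while questionnaires go to the Glasgow office (section 7). The main-trial text states no path from a questionnaire answer to PI assessment. Appendix D, section 10, does state one at 4 years: staff review every response and contact the centre about a possible SAE.

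**4. Illustration (all rates assumed).** Let true risk be *p* = 0.20 in both arms. Let detection through clinic and helpline be *s* = 0.90 in standard care and 0.50 to 0.70 in self-management, and let the shared questionnaire independently catch a proportion *q*. Then:

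recorded risk = *p* × [1 − (1 − *s*)(1 − *q*)]

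| *q* | Standard care | Self-management | Ratio | Chance of a nominally significant result favouring self-management, 165 per arm |
|---|---|---|---|---|
| 0 | 0.180 | 0.100 to 0.140 | 0.56 to 0.78 | 55% to 17% |
| 0.5 | 0.190 | 0.150 to 0.170 | 0.79 to 0.89 | 16% to 7% |
| 0.8 | 0.196 | 0.180 to 0.188 | 0.92 to 0.96 | 6% to 4% |

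With no bias, the last column would be 2.5%, half of the two-sided 5% level. The ratios do not depend on *p*; the chances do. With the same enquiry in both arms (equal *s*), the ratio is 1.00 at any *q*. The sample size does not change.

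**The case against.** The strongest reply is that the protocol already has a symmetric safety measure. Every woman completes the complications questionnaire at every time-point, section 10.1.1 says it captures AEs, and section 7.1.3 names it as a measure of safety. Table 7.2 adds unplanned contacts, GP, nurse, outpatient and inpatient care and surgery in both arms, and both arms attend at 18 months. Section 8.1 states no between-arm test of clinic-recorded AEs.

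All of that stands, and it rules out two readings that a reader might infer. One is that events in self-management are found only if the woman telephones; section 10.1.1 contradicts this. The other is that the trial's safety comparison as a whole favours self-management by design. A comparison based on the complications questionnaire is not affected by this feature.

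Some smaller points also stand. The sentences on open questioning, admissions, accidents and medicines refer to participants in general, although they follow directly on the standard-care sentence. Granulation is an expected event under section 10, recorded but not counted as an AE. Appendix C reports that all 21 centres postponed pessary clinics for at least three months, which narrowed the difference in active enquiry for that period.

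What the reply does not reach is the set of events outside the questionnaires' scope and the tissue findings between baseline and 18 months. For these, no equal route is stated.

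**Conclusion.** The point holds for clinic-recorded AEs and for interim examination findings. It does not extend to the complications questionnaire or the 18-month examination. All else equal, the expected direction is fewer recorded events in self-management, because those women are asked and examined less often.

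The size cannot be computed from the documents. The ratios of 0.56 to 0.96 rest on assumed detection rates and on independence between the clinic and questionnaire channels. They show that the bias shrinks as the shared questionnaire catches more, and vanishes only if it catches everything or if enquiry is the same in both arms. A single ratio taken from the clinic channel alone should not be read as the bias in the trial, because it ignores the shared questionnaire. The primary outcome and its sample size are unaffected.

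**What to change.** **Data collection (section 10.1.1).** Specify the same short AE question set for both arms at 6, 12 and 18 months: any admission, any professional advice sought, any new treatment. Pass positive answers to the centre for PI assessment, using the kind of route that Appendix D already sets out for possible SAEs.

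**Analysis and reporting.** Base the between-arm comparison of non-serious AEs and complications on the questionnaires and the 18-month examination. Tabulate interim clinic- and helpline-detected AEs by source, descriptively. Report all deaths and SAEs by arm from every source, with the unequal ascertainment stated. Confining these to the symmetric sources would lose deaths, and SAEs in women who did not respond.

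Appendix C says recruitment was complete when the pandemic began, and Appendix D describes the questionnaires to 18 months as completed. Where that is so, only the analysis and reporting part can still be applied.

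**Cost.** A few questionnaire items, some follow-up of answers with centres, and fewer events in the non-serious comparison. The reporting part costs only wording.

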#### **10.1.2 Recording AEs and SAEs**

When an AE/SAE occurs, it is the responsibility of the local PI to review all documentation (e.g. hospital notes, laboratory and diagnostic reports) related to the event. The local PI should then record all relevant information in the CRF and on the SAE form (if the AE meets the criteria of serious).

Information to be collected includes type of event, onset date, local PI assessment of severity and causality, date of resolution as well as treatment required, investigations needed and outcome.

### **10.1.3 Assessment of AEs and SAEs**

Each AE must be assessed for seriousness, causality, severity and expectedness by the local PI or another suitably qualified physician in the local TOPSY research team who is trained in recording and reporting AEs and who has been delegated this role.

### **10.2 Reporting responsibilities of the local PI and CI**

Once the local PI becomes aware that an SAE has occurred in a study participant, they will report the information to the TOPSY Study Glasgow Office within 24 hours. The SAE form will be completed as thoroughly as possible with all available details of the event and signed by the PI. If the local PI does not have all information regarding an SAE, they will not wait for this additional information before notifying the TOPSY Study Glasgow Office. The form will be updated when the additional information is received.

The SAE form should be transmitted by fax/email to the TOPSY Study Glasgow Office on [name]/[contact].

If, in the opinion of the local PI and the CI, the event is confirmed as being related and unexpected, the CI will submit a report to the main REC, the trial sponsor and the DMEC within 15 days of the CI becoming aware of it.

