| OUTCOMES            | 
Primary outcome measure is prolapse-specific quality of life (PFIQ-7).
 
Secondary outcomes/Questionnaires;
 
 
• Generic quality of life (EQ-5D-5L)
 
• Prolapse symptoms (PFDI-20);
 
• Sexual dysfunction (PISQ-IR);
 
• Self-efficacy (GSE)
 
• Pessary Use Questionnaire (Patterns of pessary use, acceptability and benefit)
 
• Pessary complications
 
• Pessary Confidence Questionnaire (Efficacy)
 
• Adherence to trial group; crossover to other group.
 
• Resource Use Questionnaire (for health economic evaluation)
 
 |
| CO-ORDINATION       | 
Local: by local lead Principal Investigator, an Intervention healthcare professional and a Recruitment Officer.
 
Central: by TOPSY Study Glasgow Office in Glasgow Caledonian University.
 
Overall: by the Project Management Group and overseen by the Trial Steering Committee and the Data Monitoring and Ethics Committee.
                                                                                                                                                                                                                                                                                                      |

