## **9 ORGANISATION - Trial coordination**

### **9.1 Sponsor**

Glasgow Caledonian University will now act as study sponsor and their finance department will be responsible for the financial management of the grant including agreeing contracts with collaborating institutions and submitting financial reports to HTA as required.

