## **9.5 TSC and DMEC**

An independent Trial Steering Committee (TSC) will review the study on behalf of the sponsor and the funder. The TSC will include an independent chair, clinicians with expertise in prolapse/pessary management, a member of the public and a member of the PMG; a representative from the sponsor and the funder will be invited to meetings of the TSC and minutes will be copied to the funder. The TSC will meet at least annually to supervise trial conduct to ensure the principles of Good Clinical Practice and relevant regulations are adhered to and will advise on the stop/go criteria specified in section 3.1.

A separate and independent Data Monitoring and Ethics Committee (DMEC) will be convened. This Committee will be independent of the trial organisers and the TSC. It is anticipated the members will meet once to agree terms of reference and then annually (or more frequently if required) to monitor accumulating data and oversee safety issues.

During the period of recruitment to the trial, the DMEC will review a report on accumulating safety data, together with any other analyses that the committee may request, at each meeting, and any serious adverse events reported to the DMEC as detailed in Section 10.1. In the light of this report, the DMEC will advise the Trial Steering Committee if, in its view, the trial should continue as planned, or stop early due to clear harm or benefit of a treatment, or external evidence; it may also make recommendations as to other amendments to the trial protocol based on this report.

The Chair and the other independent members of the TSC and DMEC are to be appointed after confirmation by the HTA.

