## **13. INDEMNITY**

The Participant Information Leaflet provides a statement regarding indemnity for negligent and non-negligent harm.

Pessaries have been used in the NHS for many years and are a relatively safe intervention. Self-management is a system used widely in health care and no serious ethical issues are foreseen. Potential risks relate to possible serious pessary complications, specifically: fistula, incarceration of pessary, occurrence of vaginal cancer. Incarceration of pessary, fistulae and rare reported cases of cancer are associated with the pessary not being removed and replaced for a prolonged period of time. As participants (self-management group and standard care group) are asked back to clinic at 18 months this is the longest that a participant should have a pessary in situ and very long periods without care are avoided.

Participation in the study will help evaluate the training and teaching procedures and effectiveness of self-management. Taking part in this study does not affect normal legal rights. Whether or not women take part, the same legal rights apply as any other patient in the NHS (which includes professional indemnity insurance for negligence). If a participant wishes to complain about their health care or any aspects of this study, the normal NHS mechanisms will be available.

In addition, the universities involved with the trial hold and maintain a 'no fault' insurance policy. This policy covers all employees of the universities and those working under their direction.

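### Section 10.2 requires the 15-day report of a serious event only if the local PI and the CI both consider it related and unexpected, so one dissent removes that report

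*Protocol*

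**What the plan says.** Section 10.1.3 places the assessment locally: "Each AE must be assessed for seriousness, causality, severity and expectedness by the local PI", or by a suitably qualified physician delegated at the centre.

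Section 10.2 then sets two steps. The first is unconditional. Once the local PI learns of a serious adverse event, "they will report the information to the TOPSY Study Glasgow Office within 24 hours". The second is conditional: "If, in the opinion of the local PI and the CI, the event is confirmed as being related and unexpected", then "the CI will submit a report to the main REC, the trial sponsor and the DMEC within 15 days", counted from when the CI learns about the event.

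Section 9.5 describes what the DMEC sees: during recruitment, a report on accumulating safety data at each meeting, any other analyses it asks for, and "any serious adverse events reported to the DMEC as detailed in Section 10.1". Meetings are annual, or more frequent if required. The opening of Section 10 also has concerns about procedures, participants or staff relayed to the DMEC chair, with no time limit.

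**The concern.** The local investigator knows the participant and is the person assigned to assess causality. Section 10.2 nevertheless makes the external report depend on a second opinion that must agree. If the local PI believes the intervention caused a serious event and the CI does not, the text no longer requires a report to the ethics committee or the DMEC within 15 days. The reverse holds as well. Nothing says whose opinion prevails or that a disagreement is itself reported.

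The DMEC is the independent body that advises on stopping for harm (Section 9.5). Section 13 links the gravest pessary complications to long intervals without removal, and the two arms differ in who removes the pessary and how often a clinic sees it. Prompt notice of an event that one responsible clinician considers related is therefore worth having.

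**Working it through.** The plan states no figure on this point and no statistical calculation applies. The check is a logical one, made by setting the sections side by side.

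**1. The trigger.** Let each person's answer be yes if that person considers the event both related and unexpected.

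| Local PI | CI | 15-day report as written | 15-day report with *or* |
|---|---|---|---|
| yes | yes | due | due |
| yes | no | not due | due |
| no | yes | not due | due |
| no | no | not due | not due |

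As written, one of the four patterns triggers the report; with *or*, three of the four do. These count patterns, not how often each occurs.

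**2. What remains when the report is not due.**

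- *Study office, 24 hours (10.2).* Unconditional, but this step names only the office as recipient.
- *Notice of unexpected, possibly related clinical events (9.4).* The local PI alone informs the Glasgow office, a lower threshold, but again the recipient is the office.
- *DMEC safety report (9.5).* Independent of either opinion, but tied to meetings. On the annual cycle the wait could approach 12 months. The milestones in Section 9.6 put the second DMEC at month 15 (January 2019) and the third at month 36 (October 2020): 36 − 15 = 21 months. Extra meetings are allowed.
- *Interim data (8.1).* The DMEC reviews these at its discretion and at least annually.
- *Relay of concerns to the DMEC chair (Section 10).* No time limit and no defined serious-event trigger.

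None of these gives the ethics committee or the DMEC an individual event within a stated number of days.

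**3. Expectedness.** The opening of Section 10 lists five expected events: granulation, expulsion, smell, discharge, and bleeding at pessary change. Section 10.1 names six serious events potentially associated with a pessary: entrapment, urinary retention, faecal impaction, fistula, vaginal cancer and ureteric obstruction. The two lists do not overlap, and Section 10.1 excludes from adverse-event recording only the expected events already outlined. On the protocol's own usage, the six are not expected. Sections 10.1.3 and 10.2 do not refer back to that list, so the meaning has to be inferred. If expected means only the five, relatedness becomes the deciding question for the six, and that is where the two-person condition matters.

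**4. The cross-reference.** Section 9.5 points to Section 10.1 for serious events reported to the DMEC. Section 10.1 and its subsections cover definitions, detection, recording and assessment. The only such reporting rule is in 10.2.

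**The case against.** The strongest reply is that only one channel is conditional. Every serious event reaches the study office within 24 hours. That office is described as "Central: by TOPSY Study Glasgow Office in Glasgow Caledonian University", and "Glasgow Caledonian University will now act as study sponsor", so the sponsor's institution hears of it regardless. The DMEC sees safety data whatever the PI and CI think, can ask for more and can meet early. No sentence grants the CI a veto; the dependence on agreement is a literal reading of one conjunction, and a sensible trial team might report a disputed event anyway.

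Most of this stands. For the sponsor the practical loss is small, although Section 10.2 names office and sponsor separately. For the ethics committee and DMEC, the other routes do not replace a 15-day report.

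A reader might also infer that the risks Section 13 singles out ("Potential risks relate to possible serious pessary complications, specifically: fistula, incarceration of pessary, occurrence of vaginal cancer") would be marked expected and so never reported quickly. The documents do not support this: the protocol's list of expected events contains none of them. What stands is that the link to that list should be explicit.

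Finally, this version was issued after the planned end of 18-month follow-up (July 2021). Appendix D keeps Section 10 in force for the 4-year follow-up apart from stated changes, so the rule still applies, but to less exposure.

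**Conclusion.** The point holds for the expedited report. As written, a dissent by either the local PI or the CI removes the duty to inform the ethics committee and DMEC within 15 days, and no rule deals with disagreement. The consequence is delay: from 15 days to the next DMEC meeting, nominally up to a year, or to a relay with no deadline. This rests on a literal reading of Section 10.2 and on no unscheduled meeting being called.

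A reader might go further and conclude that a serious event is hidden altogether, or that this is the only way one can reach the DMEC. Neither follows, because the 24-hour notice, the meeting reports and the relay of concerns all remain. Nor can a share of missed reports be given: the document has no figure for how often the two assessors agree, and any percentage would come from an invented one. The cross-reference error in 9.5 is clerical. Overall this is a modest wording fault in a safety rule, worth correcting because correction is cheap.

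**What to change.** - In Section 10.2, make the report due when the local PI *or* the CI considers the event related and unexpected. Add that the CI may upgrade but not downgrade the local PI's relatedness assessment.
- In Sections 10.1.3 and 10.2, state that expected means only the events listed at the opening of Section 10, so that the serious events named in Section 10.1 are not treated as expected.
- In Section 9.5, change the cross-reference from Section 10.1 to Section 10.2.

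There is no need to send all six named serious events to the DMEC whatever their relatedness; that goes beyond the fault found. The cost is a few sentences in an amendment and a few more expedited reports. The document gives no expected number of serious events, so that increase cannot be sized.
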